## Abstract

**Introduction:**

In Australia, kidney failure treatment disparities exist between Aboriginal and/or Torres Strait Islander (First Nations) and non-First Nations people. Despite persistent calls from First Nations patients with kidney failure, they are less likely to have treatment that allows them to live at home.

**Methods and analysis:**

This is a prospective, multicentre study based in Australia. The aim of the study is to characterise the socioeconomic, environmental, health service and biomedical factors driving the health outcomes and patterns of health service utilisation experienced by First Nations patients and investigate whether health service changes to address these identified barriers can achieve higher rates of renal replacement therapy at home on country. This will be achieved by mixed-methods data collection at health service (audit and process data), staff (surveys and qualitative interviews) and patient (survey testing, feedback sessions, health outcomes) levels. A process evaluation will identify barriers and enablers to health services changes in relation to cultural safety. Baseline and follow-up data will be compared to assess the extent to which health services change their service delivery and the impact on health outcomes for First Nations patients with kidney failure. Qualitative and quantitative data will be integrated to provide an in-depth understanding of project outcomes and impacts.

**Ethics and dissemination:**

This study is funded by the National Health and Medical Research Council of Australia (GNT1158075). Ethics approval has been obtained so far from the Human Research Ethics Committee (HREC) of the Northern Territory Department of Health and Menzies School of Health Research (2019-3530), Far North Queensland HREC (2023/QCH/99606 (Nov ver 4)-1732), the Central Adelaide Local Health Network HREC (2023/HRE00209), the Aboriginal Health Council of South Australia (AHREC Protocol #: 04-23-1078), the Aboriginal Health and Medical Research Council of New South Wales (AH&MRC HREC reference: 2230/24) and the Far North Queensland Human Research Ethics Committee (FNQ HREC reference: HREC/2023/QCH/99606 (Nov ver 4)-1732). Study participants, policy makers and community organisations will be provided with updates of study findings. Dissemination of study findings will be through peer-reviewed publications and conference presentations.

**Trial registration number:**

ACTRN12623001241628.

STRENGTHS AND LIMITATIONS OF THIS STUDYThis multicentre prospective study is led by a team of First Nations and non-First Nations researchers, with extensive First Nations community consultation.A focus on service-level factors (ie, policies, procedures and practices, staff beliefs and behaviours) is a particular strength of the study and will provide understanding of barriers and facilitators related to organisational change.This study is grounded in First Nations patient experiences and outcomes: culturally safe practices are defined by the patients and their communities.This study includes a participatory action component with lead clinician investigators as co-champions driving change together with patients and local communities.Evidence from this study will inform both national guidelines for the care of First Nations patients in tertiary care settings, and local improvements to care at involved sites.

## Introduction

 Kidney failure, when dialysis or a kidney transplant is required to maintain life, is a rapidly increasing global health and healthcare burden.^1^ Worldwide, access to care for patients at risk for kidney failure or in need of treatment is most challenging for those in low- and middle-income countries.^1^ While kidney failure incidence is comparatively low in high-income countries such as Australia, disparities exist between Aboriginal and/or Torres Strait Islander (First Nations) and non-First Nations people.^2^

First Nations Australians have a higher incidence of kidney failure compared with non-First Nations Australians. They have at least six times the age-standardised incidence of renal replacement therapy (RRT) of non-First Nations Australians.^2 3^ Although only 3.2% of the Australian population,^4^ almost 1 in 10 patients commencing RRT each year in Australia identify as First Nations.^2^ Among adults aged 25–64 and people from rural and remote areas, rates are up to 15 times higher.^5 6^ More than half of First Nations Australian kidney failure patients come from remote or very remote areas. (In comparison, only 1.1% of non-First Nations kidney failure patients come from remote or very remote areas of Australia.)^7^

Additionally, First Nations patients experience very different patterns of RRT. Where most non-First Nations patients with kidney failure receive treatment that allows them to live at home, the majority of First Nations patients still receive urban or regional facility-based treatment.^2 8^ Community-based dialysis or a kidney transplant allows a patient to return to live in their community.^2^ However, uptake of these modalities (community nurse-facilitated haemodialysis, self-care haemodialysis, peritoneal dialysis and kidney transplantation) among First Nations Australians continues to be low.

For over 25 years, First Nations health organisations and patients in rural and remote Australia have persistently called for more responsive treatment, closer to home, for First Nations peoples with end-stage kidney disease.^9 10^ Community-led advocacy groups have continued this call in more recent years. A national meeting of First Nations kidney failure patients in September 2017 renewed this message.^11^ Over the last 15 years, substantial progress has been made in expanding and decentralising haemodialysis care across remote Australia.^12^ Nevertheless, most treatment is still provided as haemodialysis in nurse-facilitated centres in major or regional towns, rather than at home in remote communities.^6^

Various barriers to treatment at home on country (Being at home on ‘country’ refers to the lands, waterways and seas to which First Nations peoples are connected. The term contains complex ideas about law, place, custom, language, spiritual belief, cultural practice, material sustenance, family and identity (AIATSIS 2021 https://aiatsis.gov.au/explore/welcome-country).) have been reported: remoteness, cost, the presence and severity of comorbid medical conditions, housing and environmental issues, low levels of health literacy, poor practitioner–patient communication, lack of engagement, cultural factors, practitioner-, service- and system-level biases.^13^,^15^ The physical and psychosocial demands of dialysis treatment for First Nations patients are accentuated by family separation and ineffective communication between patients and their healthcare providers.^10^ First Nations patients are often young and socially isolated when relocated from rural and remote communities to urban settings for regular dialysis treatment. Both kidney transplantation and self-care dialysis provide a superior quality of life at costs cheaper than facility-based dialysis for non-First Nations Australians. However, self-care treatment options are underused for First Nations people with kidney failure.^2 16^

International literature has demonstrated that both educational attainment and levels of health literacy correlate with access to RRT modalities such as kidney transplantation or self-care dialysis.^17 18^ First Nations RRT patients often feel that they have been excluded from information and feel poorly equipped to seek it.^19^ Qualitative research has documented concerns about poor communication between First Nations dialysis patients and non-First Nations health professionals.^1119^,^22^ Ineffective communication with healthcare practitioners is associated with poorer outcomes for First Nations patients, including confusion and frustration^19 21^; discharge against medical advice^23^ and distrust of healthcare providers.^24 25^ Interpreters for First Nations patients remain grossly underused.^26^ Furthermore, experiences of racism in the healthcare sector have been reported by First Nations Australians^27^ and have been explored qualitatively as a key reason for avoiding or refusing healthcare.^28^

Culturally safe healthcare provision has been promoted to improve healthcare outcomes for First Nations people globally.^29 30^ Cultural safety refers to: ‘the ongoing critical reflection of health practitioner knowledge, skills, attitudes, practising behaviours and power differentials in delivering safe, accessible and responsive healthcare free of racism’.^31^ Ultimately, First Nations individuals, families and communities are the ones who decide what is culturally safe.^32 33^ Moreover, organisational- and structural-level policies, practices and procedures need to promote culturally safe care to address institutional and systemic racism.^34^ The assessment of systemic and/or institutional levels of cultural safety affecting First Nations Australians is currently more challenging than the measurement of practitioner-level cultural safety. Systematic reviews of cultural safety training for health practitioners have found some improvements in practitioners’ awareness, knowledge and behaviours; however, the majority of these studies use self-reported surveys.^35 36^ While frameworks^37 38^ exist that seek to explain the role of service-, system- and societal-level biases in poorer outcomes,^39^ their measurement is still largely conceptual.^33^ Few studies have examined the effect of service- and system-level interventions,^40^ thus more high-quality research is needed and in different health settings and locations to examine the effect of system-level interventions on the provision of culturally safe healthcare.

### Study aim and objectives

The aim of the study is to characterise the socioeconomic, environmental, health service and biomedical factors driving the health outcomes and patterns of health service utilisation experienced by First Nations Australians and investigate whether health service changes to address these identified barriers can achieve higher rates of RRT closer to home. The study’s hypothesis is that service-level attributes are more important than patient factors in the association with rates of ‘returning home’ models of care, and that some service-level attributes are able to be modified to increase rates of ‘returning home’ care. An overview of Return to Country (RTC) programme logic, including hypotheses and aims, can be found in figure 1.

**Figure 1 F1:**
[figure not shown]
Return to Country—study design and programme logic.

Objectives are:

To test the feasibility, acceptability and appropriateness of a patient survey adapted for First Nations peoples (both in English and several First Nations languages).To understand the factors associated with treatment disparities (ie, in relation to transplantation and dialysis treatment) experienced by First Nations patients compared with non-First Nations patients.To assess the level of renal health services’ cultural safety from the patient perspective.To identify the barriers and enablers to organisational change in relation to the provision of culturally safe care to First Nations patients with kidney failure.To assess and evaluate the extent to which renal health services change their delivery of care to First Nations patients with kidney failure following an assessment of their level of cultural safety.To assess the impact of the renal health service-based changes on health outcomes for First Nations patients with kidney failure.

## Methods and analysis

The RTC study is a prospective, multicentre study based in Australia.

### Study setting

14 tertiary renal health services (of approximately 90) throughout Australia have been invited to take part in the RTC study. These services coordinate care for at least five new First Nations patients starting RRT each year on average, and together they care for up to 90% of First Nations patients starting RRT nationally each year. Of those, four services care for approximately 60% of all incident First Nations RRT patients, and a further four care for an additional 15–20% of incident First Nations RRT patients.^2^

### Study design

RTC is a mixed-methods project consisting of three parts as shown in figure 2.

**Figure 2 F2:**
[figure not shown]
Return to Country—study components.

### Part 1: survey testing

The objective of the first part of RTC is a test of the feasibility and appropriateness of a patient survey process to understand First Nations patient reported experiences and outcomes, including the acceptability, translatability and content validity of survey items. The RTC patient survey has five domains: ‘Demographic and Housing’; ‘Wellness’; ‘Experiences of Racism’; ‘Health Literacy’ and ‘Care and Treatment’. Survey testing will be conducted in several services located in the Northern Territory, Queensland and New South Wales to assess where differences exist for First Nations patients that predominate speaking First Nations language versus those that predominately speak English.

#### Data collection

Patient participants will be identified by a First Nations community representative and approached by the local research team. Part 1 consists of three steps, which can be found in figure 3. First, plain English survey items will be critically reviewed and modified with a sample (n=15) of language experts (including some patients receiving dialysis). Second, this version will be trialled with participants using adapted video reflexive ethnography and/or an integrated process of reflection and critical analysis as the survey is administered. The review process in the first and second step involves extensive discussion with participants and does not reflect the time and attention demands that will be involved in the typical administration of the survey. Therefore, tolerability will be explored in step III when the survey is administered as intended with recently commenced patients, within 12 months after commencing RRT. This process will be conducted in several services located in the Northern Territory, Queensland and New South Wales to assess whether differences exist between different First Nations language groups. All activities will be audio- or video-recorded.

**Figure 3 F3:**
[figure not shown]
Phases of survey development.

#### Data analysis

Data from the first two steps will be translated, transcribed and thematically analysed using an iterative and inductive process while exploring factors that influence acceptability, translatability and feasibility. This process will inform alterations to survey administration procedures and revisions of survey items. Content validity of survey items will be explored through comparison with participant responses during survey administration and comparison with peer-reviewed qualitative research of renal patient experiences. Step III will analyse tolerability by comparing patient-identified priority topics from in-depth interviews after survey administration with their survey responses. Findings of Part 1 will inform the development and use of surveys in a culturally safe way with First Nations peoples and determine whether the patient survey is used in other renal health services.

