### Study sample

Convenience and purposeful sampling will be used in the study. With all 14 invited tertiary renal services participating in the study, RTC aimed to reach an estimated 1250 renal health staff and 900 First Nations renal patients. Given delays from research moratoria due to the COVID-19 pandemic at all sites, a more targeted recruitment strategy focussing on eight sites caring for the majority of First Nations patients commencing RRT will still provide data about the care of 750 First Nations patients by an estimated 600 renal health staff.

Part 1 will be completed in four sites (Darwin, Alice Springs, Cairns and Newcastle) with between 15 and 20 patient participants per site.

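### The stated Step III analysis of survey tolerability measures content agreement, so it gives no direct evidence on the burden that Step III was set up to assess.

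*Protocol article*

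**What the plan says.** All of the relevant text is in the protocol article.

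- **Part 1, Data collection.** The first two steps involve long discussion with participants. The article says that this process "does not reflect the time and attention demands that will be involved in the typical administration of the survey". It draws the consequence directly: "tolerability will be explored in step III when the survey is administered as intended with recently commenced patients". These are patients within 12 months of starting renal replacement therapy. The same paragraph adds: "All activities will be audio- or video-recorded".
- **Part 1, Data analysis.** Data from the first two steps are analysed thematically, "exploring factors that influence acceptability, translatability and feasibility". A separate sentence covers a further property: "Content validity of survey items will be explored through comparison with participant responses during survey administration", together with a comparison with published qualitative research. The next sentence fixes the third step: "Step III will analyse tolerability by comparing patient-identified priority topics from in-depth interviews after survey administration with their survey responses". The paragraph ends by saying that the Part 1 findings will, among other things, "determine whether the patient survey is used in other renal health services".
- **Study sample.** Part 1 runs at four sites "with between 15 and 20 patient participants per site". No number is given for Step III alone.
- **Table 1 and Patient and public involvement.** For the survey-testing objective, Table 1 lists adapted video reflexive ethnography and an evaluation of feedback from patients and interpreters. The involvement section says that this feedback informs the design of the survey.

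**The concern.** The article asks one question in Step III and analyses another. The question, as the Data collection text frames it, is whether patients can manage the survey when it is given in its usual form, with the time and attention that this takes. The analysis asks whether the topics that patients raise freely afterwards match what they answered. A long and tiring survey could match the interviews well, and a short and easy one could match them badly.

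At stake is the quality of the evidence behind the decision to use the survey in other services. The survey has five domains, one of them on experiences of racism, and Step III respondents are patients who have recently started treatment. Burden is a natural question for that decision, and the investigators saw the need to test it. If the analysis is carried out as written, the step designed to answer it will report on something else under the name of tolerability.

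**Working it through.** The plan gives no figure on this point and no formula applies. The check is whether the stated analysis can inform the stated construct.

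**1. What tolerability means here.** The Data collection text gives the reason for Step III (the earlier steps do not show the demands of typical administration) and then introduces tolerability as what follows from that reason. The construct is respondent burden under intended use, and Step III is the only step assigned to it.

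**2. What is analysed.** The Data analysis text names two inputs: priority topics from the interview after the survey, and the same patient's survey responses. Neither is a measure of time, effort, fatigue, distress or completion, and none of these is named elsewhere in the Part 1 analysis.

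**3. What each result would show.**

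| Topics and responses | Possible explanations | Burden identified? |
|---|---|---|
| Agree | The survey covers what matters to the patient, whether or not it was tiring to complete | No |
| Disagree | Missing content; translation problem; reluctance to disclose in a survey; loss of attention | No, as burden is only one of several explanations |

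Neither result separates a tolerable survey from a burdensome one.

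**4. Whether another stated analysis fills the gap.**

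- Acceptability, translatability and feasibility are tied to data from the first two steps. By the article's own account, the review process in those steps does not show the demands of normal use.
- The content-validity sentence uses what participants say during administration and published research. It has a different comparator and timing from the Step III comparison, but it too concerns content.
- The patient and interpreter feedback in Table 1 may touch on burden, but no analysis of burden is attached to it.
- The recordings could yield burden information, but no such use of them is stated.

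**5. Size.** Four sites with 15 to 20 patients each give 4 × 15 = 60 to 4 × 20 = 80 patients for Part 1 as a whole. The article does not say how many of them enter Step III, so the precision of any Step III burden measure cannot be worked out.

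**6. Reach.** The patient survey is not among the five data collection steps of Part 2, nor in the Part 3 follow-up, which repeats those steps. Table 1 lists it only as the thing being tested under the first objective. No registry or outcome analysis is stated to use it.

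**The case against.** The strongest reply has four parts.

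- **This is a condensed article.** Minutes, breaks and skipped items are operational detail that a fuller protocol may hold, and Figure 3, on the phases of survey development, is not shown. It stands that the absence of such detail is no fault in itself, and that the documents do not show burden will go unanalysed. The point does not rest on absence, however. The article positively names a method for tolerability, and that method does not fit the meaning it gave the word. Further detail elsewhere would not reconcile the two sentences as written.
- **Agreement may carry some information on burden.** A tired patient may give answers that miss what the same patient later raises. This is fair, and attention is part of the article's own description. But the signal is indirect and has several other explanations.
- **The decision draws on Part 1 as a whole.** This stands. A reader might infer that the decision would be taken with no tolerability evidence at all. The documents do not support that: feasibility, acceptability, translatability, content validity and patient and interpreter feedback all contribute, and the interviews may bring up burden unprompted. What is missing is direct evidence on burden from the Step III analysis as stated.
- **Part 1 is a qualitative pilot, and stop rates impose a quantitative frame.** This stands in part. Simple description is enough; no test, threshold or target precision is needed.

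A reader might also infer that later study results are weakened, or that the Step III comparison merely repeats the content-validity analysis. Neither follows. No Part 2 or Part 3 analysis is stated to use the survey, and the two comparisons use different material at different times.

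**Conclusion.** The mismatch is real and lies in the text of Part 1. Step III is introduced to explore the time and attention demands of normal administration, but its tolerability analysis is a comparison of content. As stated, that analysis gives the decision on wider use no direct evidence on burden, while other properties of the survey are examined.

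The consequence is confined to Part 1 and that decision; the registry-based outcome analyses are unaffected. It cannot be expressed as a number, because neither a Step III sample size nor any expected rate of stopping or skipping is given.

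The conclusion assumes that tolerability carries the meaning that the Data collection text gives it, and that Figure 3 and the full protocol do not replace the stated analysis with another.

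**What to change.** In Part 1, Data analysis, replace the Step III sentence with a short statement of three elements:

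1. **Burden from the recordings already planned.** Describe the duration of administration, breaks and stops, completion, items skipped or refused in each survey domain, and interpreter use. Describe these by language group, since differences between language groups are already a stated interest of this step.
2. **Burden as the patient sees it.** Add one direct question on the effort of completing the survey to the existing interview after administration.
3. **Correct label.** Keep the comparison of interview topics with survey responses, and report it as content validity.

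It would also help to state how many patients are expected in Step III, so that readers can judge how much weight the descriptions bear.

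The cost is some coding time on recordings that will exist in any case, and one interview question. No further participants or visits are needed.
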